15. Patients with previous and current interstitial pneumonia, pneumoconiosis, radiation pneumonitis, drug-related pneumonia, severely impaired pulmonary function, etc. that may interfere with the detection and treatment of suspected drug-related pulmonary toxicity;
16. Presence of known active or suspected autoimmune disease, except for those who are in a stable state at enrollment (not requiring systemic immunosuppressive therapy);
17. History of severe chronic autoimmune diseases, such as systemic lupus erythematosus; history of inflammatory bowel diseases such as ulcerative enteritis and Crohn 's disease; history of chronic diarrheal diseases such as irritable bowel syndrome; history of sarcoidosis or tuberculosis; history of active hepatitis B and C and HIV-infected patients; patients with well-controlled non-serious immune diseases, such as dermatitis, arthritis, psoriasis, etc., can be enrolled. Patients with hepatitis B virus titer < 500 copies/ml can be enrolled;
18. Patients requiring treatment with systemic corticosteroids (at dose level > 10 mg/day prednisone efficacy) or other immunosuppressive drugs within 14 days prior to the first dose or during the study. However, enrollment is permitted if: In the absence of active autoimmune disease, patients are permitted to use topical or inhaled steroids, or adrenal hormone replacement therapy at dose level ≤ 10 mg/day prednisone efficacy;
19. Any active infection requiring systemic anti-infective treatment within 14 days before the first dose, with the exception of prophylactic antibiotic therapy (eg, prevention of urinary tract infection or chronic obstructive pulmonary disease);
20. Treatment with live vaccines within 28 days prior to the first dose; except for inactivated viral vaccines for seasonal influenza;
21. Prior treatment with antibody/drug therapy against immune checkpoints, such as PD-1, PD-L1, CTLA-4 inhibitors;
22. Treatment with related drugs or medical technology affecting immunity within 6 months prior to the first dose (including but not limited to: thymopentin, thymalfasin, interferon, CAR-T therapy, etc.);
23. Patients who are receiving other clinical study treatment, or planning to start this study treatment less than 1 month before the end of previous clinical study treatment;
24. Known history of allergy or intolerance to any study medications or their components;

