25. Patients with a history of alcohol abuse, drug abuse and drug abuse. Patients who have stopped drinking alcohol can be enrolled;
26. Patients who do not follow the doctor 's advice, do not take medicine according to the regulations, or have incomplete data that may affect the efficacy judgment or safety judgment;
27. Pregnant or lactating female patients;
28. Patients with conditions that may increase the risk of study participation and study medications, or other severe, acute, or chronic diseases that, in the judgment of the investigator, will make them inappropriate for participation in a clinical study.
29. Patients with other conditions unsuitable for this clinical trial judged by the investigator.
30. **Study Termination and Withdrawal**
    1. **Termination Criteria**

- Intolerable toxicity that does not resolve despite dose adjustment occurs, which requires discontinuation of the study drug treatment;
- During the study period, other anti-tumor treatments, or any concomitant treatment that may significantly impact the safety and efficacy of the study drug, is required;
- An adverse event or serious adverse event occurs, which requires treatment discontinuation as judged by the investigator;
- The subject experiences other new malignancies;
- The subject experiences disease progression during neoadjuvant therapy and is deemed by the investigator to obtain no further benefit from continuing the trial and is ineligible for radical surgical resection (disease progression during neoadjuvant therapy but still eligible for radical surgical resection after evaluation, with at least one completed cycle of neoadjuvant therapy, shall not be considered as study termination);
- Poor subject compliance affects efficacy and safety assessments, with no improvement after the investigator's communication;
- Major protocol violations;
- Other conditions deemed by the investigator as unsuitable for continued treatment.
  1. **Withdrawal Criteria**
- The subject or his/her legal representative withdraws the informed consent;
- Subject's loss to follow-up;
- Subject's pregnancy;
- Subject's death;
- The investigator deems it medically necessary for the subject to withdraw from the trial.

1. **Study Process**
   1. **Screening Period (≤28 days)**

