Adverse events (AEs) associated with exposure to Serplulimab may have an immunological etiology, attributable to its mechanism of action in blocking the interaction between PD-1 and PD-L1, thereby restoring T-cell activity. This may lead to hyperactive immune function, resulting in immune-related adverse events (irAEs). These irAEs may occur shortly after the first dose or months after the last dose of Serplulimab and simultaneously affect more than one body system, such as immune-related pneumonitis, diarrhea/colitis, renal insufficiency, rash, hepatitis, endocrine disorders, and autoimmune AEs like peripheral or central neuritis. Therefore, early identification and initiation of treatment are crucial for reducing complications. Based on available clinical trial data, most irAEs are reversible and can be managed by interrupting Serplulimab administration, administering glucocorticoids, and/or providing other supportive therapies. Subjects who experience the aforementioned AEs in this study should be monitored for symptoms and signs. Relevant examinations such as bronchoscopy, endoscopy, or skin biopsy should be performed to determine the etiology. If no alternative etiology is identified (such as disease progression, concomitant medications, and infections) and treatment with corticosteroids and/or other immunosuppressants is required (excluding endocrine events such as hyperthyroidism/hypothyroidism, hypophysitis, type 1 diabetes mellitus, and adrenal insufficiency, which may not require immunosuppressive therapy but are still considered to be related to the hyperactive immune function induced by Serplulimab), the aforementioned AEs should be deemed associated with hyperactive immune function caused by Serplulimab and diagnosed as irAEs. Based on the severity of irAEs, Serplulimab treatment may be temporarily suspended or permanently discontinued, and corticosteroids may be administered.

- 1. **Concomitant Medications and Concomitant Therapies**
     1. **Permitted Concomitant Medications/Concomitant Therapies**
  - Medications that are judged by the investigator to be consistent with the protocol (e.g., for treatment of disease-related symptoms and concomitant therapy for treatment-related AEs).
  - Subjects who require long-term medication due to underlying diseases such as hypertension and diabetes mellitus may continue to take the drug.

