  - Topical glucocorticoid administration, such as topical skin application, eye drops, nasal spray, inhalation, is allowed.
    1. **Contraindicated Concomitant Medications/Therapies**
  - During the treatment period of this study, subjects are prohibited from receiving the following treatments:
  - Biological therapies with anti-tumor effects (excluding cytokine drugs used to treat adverse events caused by chemotherapeutic agents), as well as traditional Chinese medicinal products with anti-tumor effects.
  - Immunomodulatory drugs not specified in this protocol, including but not limited to non-specific immunomodulators (such as thymosin, interferon, interleukin, immunoglobulin, gamma globulin) and traditional Chinese medicinal products with immunomodulatory effects.
  - Chemotherapy or targeted therapy not specified in this protocol
  - Live vaccinations within 30 days prior to the first dose of Serplulimab and during the study. Live vaccines, including but not limited to: vaccines against measles, mumps, rubella, varicella, yellow fever, rabies, BCG, and typhoid fever (oral). Vaccination with inactivated virus vaccines against seasonal influenza via injection is permitted, but live attenuated influenza vaccine for nasal spray is not allowed.
  - Corticosteroids. Inhaled corticosteroids as part of fixed treatment for asthma or chronic obstructive pulmonary disease (COPD) are permitted; corticosteroids for managing immune-related adverse events are permitted; physiological doses of corticosteroids may be approved after consultation with the sponsor.
  - Note: Prophylactic corticosteroids may be used to prevent allergic reactions (e.g., pretreatment before administration of intravenous contrast agents or chemotherapeutic drugs).
  - Subjects who, in the investigator's assessment, require any of the aforementioned treatment methods for clinical management should be excluded from the study. Subjects may receive other drug treatments deemed medically necessary by the investigator.
  - It is crucial for the investigator to review all drugs (both prescription drugs and over-the-counter drugs) that subjects receive before the study begins and at each study visit.
  - At each visit, any new drug received by subjects must be inquired about.
  - To minimize the risk of adverse drug interactions, all necessary measures must be taken to limit the number of concomitant medications that are truly necessary.

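### Section 8.7.2 makes a need for non-permitted treatment a reason to leave the study, which conflicts with follow-up of all enrolled patients and with the enrolled pCR denominator

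*Protocol*

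**What the plan says.** Protocol Section 8.7.2 opens its list with "During the treatment period of this study, subjects are prohibited from receiving the following treatments". The items are anti-tumour biological therapy and anti-tumour traditional medicines, immunomodulators outside the protocol, "Chemotherapy or targeted therapy not specified in this protocol", live vaccines, and corticosteroids. The immunomodulator item names "non-specific immunomodulators (such as thymosin, interferon, interleukin, immunoglobulin, gamma globulin" among its examples. The corticosteroid item carries its own exceptions: inhaled use for asthma or COPD, physiological doses after consultation with the sponsor, and the statement that "corticosteroids for managing immune-related adverse events are permitted". A note also allows prophylactic use against allergic reactions. A later item says that subjects who, in the investigator's view, "require any of the aforementioned treatment methods for clinical management should be excluded from the study".

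Other sections bear on the same patients:

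- **Section 5.1** makes a need for other anti-tumour treatment a termination criterion. **Section 5.2** does not name it among the withdrawal criteria.
- **Section 6.3** has all enrolled subjects monitored.
- **Section 2.2.1** counts pCR over all enrolled patients.
- **Section 12.1** defines the Full Analysis Set (FAS) as patients who received serplulimab and have one efficacy evaluation.
- **Section 8.6** says of immune-related events that "Serplulimab treatment may be temporarily suspended or permanently discontinued, and corticosteroids may be administered".
- **Section 4.3** (and the synopsis) excludes patients who need systemic corticosteroids above 10 mg/day prednisone equivalent "or other immunosuppressive drugs within 14 days prior to the first dose or during the study".

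**The concern.** Stopping study drug and leaving the study are different events. A single-arm trial needs them kept apart, because patients who stop drug for lack of effect are the non-responders and early deaths that the estimates must include. The 8.7.2 sentence merges the two. A patient who needs other anti-tumour therapy during the neoadjuvant phase may well be failing treatment. If that patient leaves, three things can follow: no efficacy evaluation, no pathology even if surgery is done later, and survival time censored at exit. Each loss depends on the outcome and tends to flatter the regimen. With 30 patients planned, each lost patient is about 3 percentage points of the sample (1/30 = 3.3%).

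**Working it through.** The protocol states no power, alpha or effect size behind the 30 patients, so there is no planned figure to reproduce. The check is mainly textual.

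**1. Who is covered.** The opening line of 8.7.2 sets the list in the treatment period, so the sentence reaches enrolled, treated patients. Unspecified chemotherapy and targeted therapy have no exception. The biological-therapy item excepts only cytokines used for chemotherapy side effects.

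**2. The same event in different sections.**

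| Section | Consequence of needing other anti-tumour therapy |
|---|---|
| 8.7.2 | Excluded from the study |
| 5.1 | Termination criterion |
| 5.2 | Not named as a reason for withdrawal |
| 6.3 | All enrolled subjects monitored |
| 2.2.1 | Stays in the pCR denominator |

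The first row cannot be followed together with the last two.

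**3. How it could reach the results.** The first scheduled on-treatment imaging falls within 7 days before Cycle 3 (Sections 6.2 and 10). With 21-day cycles given on time, Cycle 3 starts 2 × 21 = 42 days after the first dose, so imaging falls at 42 − 7 = 35 to 42 days. Assuming that the FAS evaluation means an on-treatment assessment, a patient excluded earlier for other therapy may have none. Section 10 requires an evaluation at discontinuation only for intolerable toxicity, when none was done in the preceding 4 weeks. Section 2.2.2 censors overall survival at last follow-up or last confirmed survival, and censors DFS when treatment after the trial begins. Ending follow-up at exclusion would therefore censor patients for a reason related to their prognosis.

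**4. Steroids and other immunosuppression.**

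- Steroids for immune-related events: permitted in 8.7.2, consistent with 8.6. The 8.2 table, which looks at whether steroids are down to 10 mg/day or less within 12 weeks after the last dose, assumes such patients are still observed.
- Steroids for Grade 3 or 4 infusion reactions: listed as a treatment option in 8.3, where the consequence is to stop study drug. The 8.7.2 steroid item has no exception for this use.
- Other immunosuppressants for immune-related events: foreseen in 8.6. Section 8.7.2 bars immunomodulators outside the protocol, immunoglobulin among them, with no exception for these events.
- The steroid criterion in 4.3 extends into the study and excepts only topical, inhaled and replacement use, which does not match 8.2, 8.6 or 8.7.2.

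**5. Illustration of size.** Assume 6 pCR among 30 enrolled, in line with the roughly 20% that the Background gives for existing regimens. Let k be the number of non-responders lost, so the rate is 6/(30 − k), with exact (Clopper-Pearson) 95% intervals:

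- k = 0: 6/30 = 20.0% (7.7 to 38.6)
- k = 1: 6/29 = 20.7% (8.0 to 39.7)
- k = 2: 6/28 = 21.4% (8.3 to 41.0)
- k = 3: 6/27 = 22.2% (8.6 to 42.3)
- k = 6: 6/24 = 25.0% (9.8 to 46.7)

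Both the 6 and k are assumptions. With the denominator in 2.2.1, the rate is 6/30 = 20.0% whatever k is.

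**The case against.** The strongest reply is that leaving the study is not leaving the analysis. No section deletes an excluded patient's data, pCR is over all enrolled patients, and the flow chart records adverse events and survival status at treatment discontinuation. This stands for pCR if 2.2.1 is followed. It does not settle the matter, because 12.1 makes the intention-to-treat population primary but builds the FAS on having an efficacy evaluation. Any loss from the FAS or safety set also comes largely from those set definitions; the 8.7.2 sentence adds to it by ending the visits that would qualify a patient. Nor is 8.7.2 the only exit: Section 10 has progressing patients who do not continue treatment discontinue the study.

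A second reply is that the sentence could be an entry rule, since the vaccine item reaches back before the first dose. The opening line places the list in the treatment period, so this reading is at best partial.

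Three stronger readings are tempting, and the documents do not support them:

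- **That patients given steroids for immune-related events are removed.** The same list permits that use and prophylactic use, and 8.7.1 allows treatment of treatment-related events. The natural reading is that only non-permitted uses trigger exclusion. For the same reason these patients are not in doubt for the Per-protocol Set.
- **That two entry criteria remove enrolled patients later.** The steroid criterion, and the one on patients who "do not take medicine according to the regulations, or have incomplete data that may affect the efficacy judgment or safety judgment", are worded loosely. But the synopsis presents the list as reasons not to enrol, and the flow chart checks it only at screening. On-study non-compliance has its own entry in 5.1.
- **That toxicity vanishes from the safety results.** If 4 of 30 patients had steroid-treated immune events (13.3%), a reader might fear 0/26. That would require discarding treated patients' safety data, which no section directs.

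**Conclusion.** The point holds in a limited form. For non-permitted treatments, chiefly unspecified anti-tumour therapy, 8.7.2 sends an on-treatment patient out of the study where 6.3 and 2.2.1 keep that patient in, and it sits badly with 5.1 and 5.2. The risk is outcome-dependent loss from the FAS, when exit comes before the first evaluation, and from survival follow-up. The documents give no basis for its size. The illustrated rise from 20.0% to between 20.7% and 25.0% needs 1 to 6 assumed removals and a shrunken denominator, and the protocol states no success threshold that such a shift would cross. Separately, the wording is unclear for steroids given for infusion reactions, for other immunosuppressants or immunoglobulin given for immune-related events, and for the reach of the steroid entry criterion into the study period. These are inconsistencies to reconcile and do not show that patients are removed.

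**What to change.** - **Section 8.7.2:** replace the exclusion from the study with wording that the treatment is recorded and that, whatever is decided about study drug, the patient stays in follow-up (surgery and pathology if performed, safety, survival) and in the enrolled denominator, counted as no pCR if there is no pathology. Say that the sentence covers only non-permitted uses.
- **Sections 5.1, 5.2, 6.3 and 10:** use the same distinction between stopping study treatment and leaving the study.
- **Section 4.3 and synopsis:** state that entry criteria are applied at screening and do not remove enrolled patients for later events.
- **Steroids and other immunosuppressants:** reconcile 4.3 and the synopsis with 8.2, 8.3, 8.6 and 8.7.2. Which uses are allowed is a clinical decision for the sponsor.

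The cost is a wording amendment and continued follow-up of a few patients. A few patients with confounding treatment would stay in the primary population, and the Per-protocol Set can still omit them.

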**Diagnosis, symptoms, and signs**

If a diagnosis has already been established, the diagnosis rather than individual symptoms and signs should be recorded on the CRF (e.g., record hepatic failure instead of jaundice, transaminases increased, and flapping tremor). If the symptoms and signs cannot be definitively attributed to this diagnosis at the time of reporting, they should be recorded as separate AEs/SAEs. If it is determined that the symptoms and signs are caused by the diagnosis, only the diagnosis should be reported alone, with the symptoms and signs being included in the diagnosis. For AEs, records of symptoms and signs should be deleted; for SAEs, follow-up update reports must be submitted.

**Adverse events secondary to other events**

Generally, for AEs secondary to other events (e.g., caused by other events or clinical sequelae), the primary events should be recorded, unless the secondary events are serious or constitute SAEs. However, clinically significant secondary events should be recorded as independent AEs in the CRF if they occur at different times from the primary events. If the relationship between events is unclear, the events should be recorded separately in the eCRF.

**Persistent or recurrent adverse events**

Persistent AEs refer to those that continue to exist without resolution between two evaluation time points for subjects. Such AEs should be recorded only once in the CRF. The initial severity of the event should be recorded and updated when the event worsens to document the highest severity.

Recurrent AEs refer to those that have resolved between two evaluation time points but subsequently recur. The occurrence of such events should be recorded separately in the CRF.

**Abnormal laboratory findings**

Clinically significant abnormal laboratory findings should be reported as AEs. The investigator is responsible for reviewing all abnormal laboratory findings and making a medical judgment on whether each laboratory abnormality should be reported as an AE.

**Death**

All deaths occurring during the entire study, including the 30-day follow-up period after the last dose, regardless of their relationship to the study drug, should be recorded in the Death Report Form of the CRF and promptly reported to the sponsor.

When recording death events, if the cause of death is clearly identified, the cause of death shall be documented as an AE, with the outcome of the AE being death, and the event shall be reported as a SAE (deaths due to tumor progression or deaths occurring 30 days after the last dose that are considered not related to the study drug, and are not recorded or reported as AEs/SAEs; however, the investigator shall document the death in the Death Report Form of the CRF and promptly notify the sponsor). If the cause of death is unknown at the time of reporting, it shall be recorded as "death of unknown cause" in the Adverse Event Form of the CRF, and "death of unknown cause" shall initially be reported as an SAE, followed by further investigation to determine the exact cause of death.

